#### HRV data analysis.

From the heart rate registration, we will calculate the low frequency / high frequency (LF/HF) rate of HRV, as a measure of sympatethic and parasympatethic contribution [24] at the time points indicated in 1–7.

#### SCA data analysis.

SCA magnitude and frequency will be calculated in Satori (mother) and MedStorm software (infant), at the specified time points 1–7.

#### Assessment of infant pain.

Assessment of pain signals in the infant will be done by scoring from the video recordings of the infant’s face. BIIP will be used, which scores infant state, five facial expressions and two hand actions [48].

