#### Procedure*.*

Testing will be conducted in a calm lab environment, and the infants will be fed and have a dry diaper before the equipment is applied. Before testing, the researchers will guide the mothers verbally on how to sing a song of their own choice, which can be a song of kin that is a personalized song meaningful to the mother aiming to foster bonding, reduce stress, and improve physiological stability in infant and mother, or a traditional children’s play song. The mother is instructed to hum and sing with or without words in a positive, joyful expressive affect in her prosody, using a steady, repetitive and predictable pulse in her song, singing with a smiling exaggerated expression in her face to capture her infant’s attention, striving to establish a mutual gaze and eye-to-eye interaction with her infant, accentuating the singing rhythm in her affectionate touch (if applicable), overall to sensitively adjust and match her singing style and her multimodal communications (auditory-prosodic, visual-facial, and tactile-gestural nonverbal communications) to her infant’s cues, responses, and state, aiming to create a positive affect in the dyad with her interactive multisensory stimulation and regulation. The equipment is first attached to the mother and then to the infant, ensuring good signal quality and minimizing disturbance of the infant. To synchronise measurements (fNIRS, SC, HRV, eye tracking, and video) we will verbally announce the time-points 1–7, and simultaneously manually mark the events in the equipment with keyboard markers (Fig 1). The mother and infant will then sit together in a comfortable chair in skin-to-skin position for baseline registration lasting 5 minutes (1). When we have steady-state signals and a stable baseline, the mother will start singing (2) and she continues singing for 3 minutes. After that, she offers the infant to breastfeed (3). After another 3 minutes, or until the baby has a good grip on the breast, a nurse will search for a vein (4) and perform the venepuncture (5), while the mother continues to sing and breastfeed until blood collection is ready (6). Finally, 5 minutes of signal will be registered after the blood sampling is finished (7). Before regular data collection begins, two pilot tests were conducted to calibrate the equipment and time intervals.

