**Fig 2 pone.0353856.g002:**
[figure not shown]
Infant (left) and mother (right) montage of fNIRS-optodes. Red = transmitter, blue = detector, circle = short channel. The mother montage is set to cover the following regions of interest: prefrontal, posterior frontal, parietal, and temporal regions of the brain including the right and left temporoparietal junction. The infant montage will cover the whole head and thus the same regions.

Oxygenated haemoglobin and deoxygenated haemoglobin (Oxy-Hb & Deoxy-Hb) will be registered for all channels in real-time using Aurora fNIRS and stored on a computer. The sampling rate will be set between 5 and 10 Hz using multilevel illumination.

Electrodes for registration of heart- and respiratory rate in the mother will be connected via a NIRxWINGS module (NIRx Medical Technologies) and registered in Aurora fNIRS. The infant will be attached to ECG-electrodes connected to a patient monitor (Philips IntelliVue X3, Eindhoven, NL).

From the heart rate (HR) registration heart rate variability (HRV) will be calculated. Electrodes for registration of skin conductance activity (SC) will be attached to the palmar side of the hand of the mother and connected via a NIRxWINGS module and registered in Aurora fNIRS. The infant will wear electrodes to record SC on the sole of the foot. The signal will be registered in GSR recording software (MedStorm, Oslo, Norway).

Two video cameras will be used, one to record the mother-infant interaction, later used for microanalysis of the live singing and social interactions [47], and one directed on the infant’s face, for later pain-scoring with the Behavioral Indicators of Infant Pain (BIIP) [48]. The mother will wear Tobii Pro 3 eye-tracking glasses to record her gaze at the infant [27].

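### BIIP is to be scored from video of the infant's face, which does not provide for its two hand actions, and feeding begins part-way through the recording, so the completeness of the score and its comparability across phases are at risk

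*Protocol article*

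**What the plan says.** **Source of the score.** Assessment of infant pain names one source: "Assessment of pain signals in the infant will be done by scoring from the video recordings of the infant’s face". The content of the scale follows at once: "BIIP will be used, which scores infant state, five facial expressions and two hand actions".

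**Cameras.** Measurements and instruments describes two video cameras. One is "one to record the mother-infant interaction, later used for microanalysis of the live singing and social interactions [47". The other is "one directed on the infant’s face, for later pain-scoring with the Behavioral Indicators of Infant Pain (BIIP) [48".

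**Sequence.** Under Procedure, baseline and singing come first (markers 1 and 2), and the breast is then offered (marker 3). The nurse searches for a vein (marker 4) and goes on to "perform the venepuncture (5), while the mother continues to sing and breastfeed until blood collection is ready (6".

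**Analysis windows.** The Data analysis plan sets seven points for recorded data in general. Point 3 is taken once feeding is established, point 5 directly after the skin is punctured, and points 6 and 7 about 30 seconds and 2 minutes 30 seconds after sampling has ended.

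**Use of the score.** The third hypothesis relates the neurophysiological responses to the infant's pain reaction. BIIP is the only instrument named under Assessment of infant pain.

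**The concern.** There are two separate problems.

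The first is a mismatch in the text. The scale has hand items, but both places that name its recording point to a view of the face. If the plan is followed as written, nobody is told to make sure the hands are filmed or to look elsewhere for them. Footage that leaves the hands out cannot be recovered later.

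The second is what happens to the facial items once feeding starts. The Introduction, under Synchrony for pain alleviation, singles out the mouth area as an important site of behavioural pain response. A feeding infant has that area at the breast. Every dyad follows the same order, so feeding status and phase change together and no later analysis of these data can separate them. If the score shifts between points 2 and 3 because items can no longer be read, and synchrony shifts between the same points for its own reasons, the two will be associated without pain having played any part. With 20 dyads recruited and at least 11 expected to be analysable, there is little room to detect or correct this afterwards.

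**Working it through.** The article gives no figure to reproduce on this point. The check compares its sections and counts items.

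**1. Components and stated source**

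| Component (Assessment of infant pain) | Count | Covered by video of the face as described? |
|---|---|---|
| Infant state | 1 | Taken as yes |
| Facial expressions | 5 | Yes, when not obscured |
| Hand actions | 2 | Not provided for |

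Total: 1 + 5 + 2 = 8. Hand share by count: 2/8 = 25%. This counts components and is not a share of the score, because the article gives no item weights.

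**2. Whether another section supplies the hand items**

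- Measurements and instruments gives the second camera to microanalysis.
- Assessment of video recordings uses the footage and eye tracking to log interaction, infant state and events bearing on pain behaviour. It does not mention BIIP or its hand items.
- No section describes the field of view of the face camera.

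**3. Feeding status at each analysis point**

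| Point | Planned moment | Feeding |
|---|---|---|
| 1 | Baseline | Before feeding |
| 2 | Singing | Before feeding |
| 3 | Feeding established | During |
| 4 | Search for a vein | During |
| 5 | Directly after puncture | During |
| 6 | About 30 seconds after sampling | Not stated |
| 7 | About 2 minutes 30 seconds after sampling | Not stated |

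The documented feeding points are therefore 3, 4 and 5, which is 3 of 7.

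**4. What each problem does to a comparison between phases**

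Let *k* be the number of the five facial items that cannot be read during feeding. The article does not list these items, so *k* is unknown and can only be bounded: 0 to 5. Suppose, as the worst case for the hands, that they are never in frame.

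- Readable components at points 1 and 2: 8 − 2 = 6.
- Readable components at points 3 to 5: 8 − 2 − *k* = 6 − *k*.
- Difference, before feeding against during: 6 − (6 − *k*) = *k*.
- Difference, point 3 against points 4 and 5: (6 − *k*) − (6 − *k*) = 0, if the same items are obscured throughout feeding.

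The two hand items cancel from both differences. Losing them at every point makes the score incomplete but does not in itself make phases incomparable. Comparability depends on *k*. If unread items are entered as zero, the highest attainable score is lower during feeding whenever *k* is above 0. If they are entered as missing, it is not lowered in that way.

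One further item-level difference is possible. From marker 4 the nurse handles an arm, so one hand may be less free at points 4 and 5 than at point 3. That is why the fix refers to the free hand.

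**The case against.** The strongest reply is that this is a gap in wording. A camera pointed at the face may still have the hands in frame. The second camera films the dyad and could supply the hand items without new equipment. Rules for items that cannot be scored are the kind of detail an article leaves to a fuller protocol or scoring manual. The five facial items are not listed, so nothing in the article shows that feeding hides any of them. BIIP is neither the primary nor a named secondary outcome, and the Statistical analyses section describes no comparison of BIIP between phases.

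Most of this stands as a limit on what can be claimed. A reader might infer any of the following, and the article supports none of them:

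- **That the hand items cannot be observed at any point.** The field of view is not given.
- **That scores are already known to be incomparable.** The number of mouth-related items and their visibility at the breast are not stated, and a constant loss of hand items would cancel.
- **That four of the seven points, 3 to 6, are affected.** Point 6 falls after sampling, and feeding at that time is not stated.
- **That the score has a lower ceiling during feeding and the drop will be read as pain relief.** The first part needs unread items to be scored zero. The second needs a contrast between phases that the article does not describe.
- **That BIIP is the only pain-related measure.** The Introduction also treats skin conductance and heart rate variability as reflecting pain or stress. BIIP is the only behavioural pain scale named.

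The reply does not remove the mismatch. The article does more than leave the source of the hand items open: it names the face recording in two sections and gives the other camera a different job. That is a statement needing correction, and its consequence is fixed once recording starts.

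**Conclusion.** The point holds as a mismatch in the stated source and a risk to comparability.

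- **Established from the text:** the recording named for BIIP does not provide for 2 of its 8 listed components, and feeding status differs between points 1–2 and points 3–5, the latter including the venepuncture.
- **Risk, not established:** that facial items are obscured or altered by sucking. Its size is *k* items, anywhere from 0 to 5, and it rests on the assumption that some of the five involve the mouth area.

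What is exposed is the third hypothesis, through the correlation of the pain reaction with the neurophysiological responses. The primary analysis of interbrain synchrony does not depend on it. The change should be made, and made before the first dyad, because unfilmed hands cannot be scored afterwards.

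**What to change.** Before the first dyad is recorded:

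1. **Source of the hand items.** Either frame the BIIP camera to include the infant's free hand, or score the hand items from the interaction camera that is already planned. If video was kept from the two pilot dyads, it will show which is practicable.
2. **Text.** Amend Measurements and instruments and Assessment of infant pain so that both name the recording used for face, state and hand items.
3. **Scoring sheet.** For each item and window, record scorable or not scorable. Treat an unscorable item as missing, never as zero.
4. **Reference window.** Where BIIP is compared across phases, use point 3 (feeding, before the nurse's touch) as the reference for points 4 and 5. Feeding is then the same on both sides. Do not extend this to points 6 and 7 unless feeding status there is recorded and matches.

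Cost: a camera adjustment, two amended sentences and an extra column on the scoring sheet. A wider frame gives slightly less facial detail, and item-by-item marking adds a little scoring work. Nothing in the care of mother or infant changes.

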#### Assessment of video recordings.

Social and musical interaction between the mother and the infant will be analysed with in-depth analysis of video footage and eye-tracking recordings [47]. There is a long tradition in developmental psychology research of studying parent-infant moment-to-moment interactions and communication using video recordings and microanalysis. Following the tradition, the researchers in this study will perform a hand-coded, second-by-second microanalysis of the naturalistic mother-infant moment-to-moment musical, vocal, verbal and non-verbal communication. In the microanalysis, researchers will log micro-interpersonal, interactive processes and details, as well as subtle occurrences and changes in the mother-infant musical and non-musical behaviors in relation to the parent-led pain management, the skin puncture and contextual elements in the environment. Events that are interesting to look for include those related to singing, such as changes in song, pitch, key, volume, or tempo. Events that have an impact on the infant’s pain behaviour, on infant’s overall behaviour/reactions, on the parent’s reactions, on infant’s state, including regulatory mother-infant behaviors will also be logged into an excel sheet as described in Ullsten et al., 2017 [47]. Validity will be secured through a thorough and systematic process, analysing each of the videos until no new details will be discerned. Validity will also be secured through an inter-coding peer review process between the researchers.

#### Statistical analyses.

The primary hypothesis, interbrain neural synchrony, will be analysed using General Linear Mixed Models (GLMM) and WTC [20] for both Oxy-Hb and Deoxy-Hb. After preprocessing of the signals, an interpersonal comparison will be performed for each region of interest and each time point, within each dyad. The false discovery rate (FDR) will be set to 0.05.

For the secondary outcomes, SC and HRV, synchrony will be analysed at the time points within each dyad before calculating means or medians on the group level. All statistical analyses will be done using parametric statistics (means, standard deviations, t-test or ANOVA) for data that are normally distributed and non-parametric statistics (median, inter-quartile range, Mann-Whitney or Kruskall-Wallis) for data that are not normally distributed. Chi-square test will be used to compare group distributions.

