### Sample, setting and procedure

#### Study participants*.*

Twenty mothers and their healthy newborn infants will be recruited among birthing mothers in Örebro county, Sweden. Inclusion criteria: healthy mothers above 18 years of age, able to understand Swedish or English language, having had a vaginal delivery; infants with gestational age above 37 + 0, birth weight above 2 500 g, and Apgar score at 1 minute above 7. Exclusion criteria: infants who received analgesics or sedatives within 24 hours before the blood sampling, or who failed at the newborn hearing screening test. The number of mother-infant dyads was motivated from previous studies using fNIRS during heelstick (Bembich 2022: 16 dyads [40]; Bembich 2018: 20 dyads in each group [43]), and from the above-mentioned ongoing music therapy study in Switzerland [33,34]. The sample size was determined using a Minimum Effect Size of Interest (MESI) analysis (G-Power 3−1, Heinrich Heine University, Düsseldorf, Germany) [44]. Effect size 0.35, alpha 0.05, beta 0.80, 7 repeated measurements, revealed a sample size of 11 dyads. To compensate for attrition, we will recruit 20 dyads and the pilot test with two dyads indicates that both recruitment and the recording procedures are feasible and easily tolerated by the mother and the infant. The initial recordings will help in optimising all recordings to get an analysable sample of at least 11 dyads. The mother and infant will be studied during the ordinary blood sampling for metabolic screening, done by venepuncture, i.e., no extra pain will be inflicted.

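### A normality check on 11–20 dyads decides how skin conductance and HRV are summarised and tested; one repeated-measures analysis per outcome should be fixed in advance instead

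*Protocol article*

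**What the plan says.** All of this is in the protocol article.

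- **Statistical analyses.** The closing rule is worded to cover every statistical analysis. It calls for "parametric statistics (means, standard deviations, t-test or ANOVA) for data that are normally distributed and non-parametric statistics" in the other case, the second branch being "median, inter-quartile range, Mann-Whitney or Kruskall-Wallis) for data that are not normally distributed". For skin conductance (SC) and heart rate variability (HRV), "synchrony will be analysed at the time points within each dyad before calculating means or medians on the group level".
- **Statistical analyses, opening sentence.** "The primary hypothesis, interbrain neural synchrony, will be analysed using General Linear Mixed Models (GLMM) and WTC". The primary hypothesis therefore has its own named method, with the false discovery rate set at 0.05.
- **Study participants.** "Effect size 0.35, alpha 0.05, beta 0.80, 7 repeated measurements, revealed a sample size of 11 dyads". Then "To compensate for attrition, we will recruit 20 dyads", with the aim of an "analysable sample of at least 11 dyads".
- **HRV data analysis and SCA data analysis.** The LF/HF ratio and the SC magnitude and frequency are computed at time points 1 to 7.
- **Hypotheses.** The second hypothesis expects HRV and SC to show synchrony corresponding to that in the brain signals.

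**The concern.** The rule is part of the stated method, so this is not a gap that an unseen analysis plan would fill. It makes the choice of estimand (mean or median) and of test depend on the data being analysed.

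With 11 to 20 dyads, a normality check on one value per dyad says little. It will often pass skewed data, and two samples from the same distribution will often receive different labels. Ratios such as LF/HF and magnitudes such as SC peaks are plausibly right-skewed, which is where the check is least dependable.

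Two things are at stake. One is power, because the switch often leads to an analysis less efficient than one on a well-chosen scale. The other is legibility. If labels are assigned point by point, an apparent step between neighbouring time points may be only a change from mean to median, and the plan does not say which across-time test applies when the labels disagree.

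**Working it through.** **Inputs from the article.** 11 to 20 analysable dyads; 7 time points; effect size 0.35; alpha 0.05; power 0.80 (printed as beta).

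**Assumed inputs.** The article names no normality test and gives no distribution. I took Shapiro-Wilk at 5%, log-normal values with log-SD 0.4–0.8, and correlation 0.5 between time points on the log scale. All seven points share one distribution, so any disagreement in labels is chance.

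**1. The plan's own figure.** I used one-group repeated-measures ANOVA with f = 0.35 and m = 7: λ = f²·n·m·ε/(1−ρ), df1 = (m−1)ε, df2 = (n−1)(m−1)ε. Neither ρ nor ε is stated.
- ρ = 0.5, ε = 0.75, n = 11: λ = 0.1225 × 11 × 7 × 0.75/0.5 = 14.15, df 4.5 and 45, power 0.809.
- ρ = 0.5, ε = 1: n = 10 suffices (power 0.851), and n = 11 gives 0.892.

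The figure of 11 dyads is reproduced under plausible assumptions. It belongs to a within-dyad repeated-measures analysis.

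**2. How often the check detects skew** (3,000 simulated data sets per setting in the main runs; ranges over log-SD 0.4–0.8).

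| Dyads | Skew flagged at a time point | Skew missed |
|---|---|---|
| 11 | about 20–53% | about 47–80% |
| 20 | about 38–84% | about 16–62% |

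These rates apply to a check on one value per dyad. A check on residuals pooled over the seven points would use more values and detect more.

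**3. How often seven points receive mixed labels, if each is checked separately.** About 66–96% over the same settings. Outside that range:
- Truly normal data: about 32% at n = 11 and 30% at n = 20. For seven independent checks, 1 − 0.95⁷ = 30.2%.
- Log-SD 0.3: 61% at n = 11 and 81% at n = 20.
- Log-SD 1.0: 90% at n = 11 and 37% at n = 20, because almost every point is then flagged.

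If one decision is made per outcome, the figure is 0.

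**4. Type I error.** Two time points were compared by paired t-test or signed-rank test, chosen by Shapiro-Wilk. The error rate was 3.7–5.8%, close to nominal.

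**5. Power at n = 11.** For an effect at which a pre-specified log-scale repeated-measures analysis has power of about 0.78–0.79, a normality-switched repeated-measures analysis has about 0.70–0.72. Switching between the independent-group tests that the article names gives about 0.27.

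I repeated this at the plan's effect size, taking 0.35 as Cohen's f on the log scale with ε = 1, for linear, broad-peak and single-peak time courses (1,500 runs each). The switch was between raw-scale repeated-measures ANOVA and the Friedman test. Power was 0.88–0.90 for the log-scale analysis (step 1 gives 0.892), 0.77–0.83 for the switched one, and 0.34–0.42 for the independent-group tests. Whether the switch was triggered by any single time point or by pooled residuals made almost no difference.

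**The case against.** **The unit of decision is not stated.** A reader might infer that the same outcome will be handled differently at different time points. The article does not say so. ANOVA and Kruskal-Wallis compare several sets of values at once and, run across the seven points, need one label per outcome. This objection stands: the 66–96% figure is conditional on a point-by-point check.

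**The simulated quantity is not the planned one.** The group summary is of a within-dyad synchrony measure whose form is not given, whereas the simulation uses raw levels. This also stands. The percentages illustrate LF/HF and SC levels and are not a forecast for the synchrony index. A log transform may be undefined for that index.

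**A reader might infer that choosing the test from the data inflates the false-positive rate.** The calculation does not bear this out: with a paired switch the error stays near 5%.

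**Such detail belongs in a full analysis plan.** This holds for the normality criterion and the unit of decision, and I do not count their absence. It does not cover the rule itself, which the article states.

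**The clearer defect is that Mann-Whitney and Kruskal-Wallis are for independent groups.** That is a fair but separate point. Replacing them with paired tests would leave the normality switch in place.

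**Conclusion.** The concern holds in a limited form. The article lets the observed distribution decide how the SC and HRV results are summarised and tested, and 11 to 20 dyads cannot support that decision. Under the stated assumptions, a check on one value per dyad misses the skew in about 47–80% of samples of 11. If it is made at each time point, chance alone splits the seven points in about 66–96% of data sets.

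The cost is power (roughly 0.70–0.72 against 0.78–0.79 at 11 dyads in the main comparison) and an inconsistent time course. There is no sign of an inflated type I error.

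The primary hypothesis is assigned to mixed models and wavelet coherence, so the point concerns the secondary outcomes, although the rule's wording blurs that boundary. It should be changed before analysis but does not threaten the main result. The figures depend on assumed log-normality, correlation 0.5 and Shapiro-Wilk at 5%. The direction depends only on the small sample and on at least mild skew.

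**What to change.** Delete the rule that switches on normality and state the following for each secondary outcome:

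1. One summary and one analysis covering all seven time points: a mixed model with a random dyad effect.
2. A scale chosen in advance from the nature of the measure: log for raw LF/HF and SC magnitude, and a scale suited to the synchrony index once that index is defined (Fisher z, for example, if it is a correlation).
3. Checks on model residuals only, which do not change the primary method for that outcome.
4. One within-dyad rank or permutation analysis, applied to all points, as a sensitivity analysis.

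The chance of mixed methods across the time course then falls to 0. The cost is a change of wording and an early decision on the form of the synchrony index. No data collection changes, and the Status and timeline section places analysis in 2028, so there is time. The one drawback is that summaries on a transformed scale, such as geometric means, are slightly less familiar to readers.

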## Abstract

Protecting infants’ vulnerable brain during repeated painful procedures like blood-sampling and immunizations in early life is a top priority in neonatal health care. Use of parent-delivered pain management may safeguard the infant brain but at the brain level, it is still unclear what drives the analgesic effect of parent-led interventions such as skin-to-skin contact, breastfeeding, and the parent’s live singing. The objective of this study is to advance our understanding of the neural mechanisms behind parent-led pain management in newborn pain care. Twenty mother-infant dyads will be studied during a planned blood sampling venepuncture, with skin-to-skin contact, breastfeeding, and the mother’s live singing. The potential interbrain synchronous cerebral activation in cortical regions of interest will be registered using functional Near-Infrared Spectroscopy (fNIRS) hyperscanning. Secondly, registration of skin conductance, heart rate variability, and the mother’s gaze will be registered. Social and musical interactions will be studied using microanalysis, as will pain using the Behavioral Indicators of Infant Pain (BIIP). The Swedish Research Ethical Review Authority has approved the study (Dnr 2025-02283-01).

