### Hypotheses

Changes in oxygenated haemoglobin (Oxy-Hb) and deoxygenated haemoglobin (Deoxy-Hb) in the prefrontal, posterior frontal, parietal and temporal areas in both hemispheres of the brain in mothers and infants will be synchronously activated, during an intervention with skin-to-skin contact, breastfeeding, and parent’s live singing during venepuncture for blood sampling.Corresponding synchrony will be seen in heart rate variability and skin conductance activity.The neurophysiological responses are correlated to the infant’s pain reaction, parent’s gaze, and social and musical interactions.

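### The named non-parametric and chi-square tests are for independent groups, but the study follows one group of dyads over seven time points

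*Protocol article*

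**What the plan says.** The design has a single arm. The Abstract states: "Twenty mother-infant dyads will be studied during a planned blood sampling venepuncture". No comparator group appears anywhere, and the Data analysis plan lists seven time points at which each dyad's recordings are analysed.

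The sample size in Study participants is built on that structure: "Effect size 0.35, alpha 0.05, beta 0.80, 7 repeated measurements, revealed a sample size of 11 dyads". Twenty dyads are to be recruited so that at least 11 can be analysed.

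The Statistical analyses section assigns mixed models and wavelet coherence to the primary hypothesis. For skin conductance (SC) and heart rate variability (HRV), synchrony is worked out within each dyad and then summarised over dyads. A general sentence follows. Normally distributed data get the t-test or ANOVA, with no statement of whether these are paired. Other data get "non-parametric statistics (median, inter-quartile range, Mann-Whitney or Kruskall-Wallis) for data that are not normally distributed". The section closes with: "Chi-square test will be used to compare group distributions". Neither the Wilcoxon signed-rank test nor the Friedman test is named.

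**The concern.** Mann-Whitney compares two independent samples and Kruskal-Wallis compares several. Here the seven sets of values come from the same dyads, so a comparison of time points is a within-dyad comparison. Even after mother and infant have been reduced to one synchrony value per dyad and time point, that value is still repeated seven times.

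An independent-samples test leaves the stable differences between dyads in the error term. If values from one dyad are positively correlated, the test's reference distribution is too wide and its p-values are too large. A real change around the puncture in SC, HRV or pain score could then be reported as absent. The non-parametric branch may well be used, since a sample of 11 to 20 dyads gives little assurance of normality.

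The chi-square sentence has a simpler problem: the article defines no groups whose distributions could be compared.

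**Working it through.** **Inputs from the article.** Effect size 0.35, alpha 0.05, 7 measurements, 11 dyads (Study participants); 20 dyads recruited. The article writes "alpha 0.05, beta 0.80, 7 repeated measurements"; the 0.80 is read here as power. The effect-size metric is not named and is read as Cohen's f.

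**Assumptions.** The within-dyad correlation rho is not given; 0.3, 0.5 and 0.7 are used, with equal correlation between all time points. The sphericity factor epsilon is 1 unless stated.

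**Step 1: reproduce the article's figure.** For a one-group repeated-measures F test with m time points and N dyads, the noncentrality is lambda = f² × N × m × epsilon / (1 − rho), with (m − 1) × epsilon and (N − 1)(m − 1) × epsilon degrees of freedom.

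- N = 11, rho = 0.4: lambda = 0.1225 × 77 / 0.6 = 15.72 on 6 and 60 df, power 0.82. Here 11 is the smallest sufficient N.
- N = 11, rho = 0.5, epsilon = 0.75: lambda = 0.1225 × 77 × 0.75 / 0.5 = 14.15, power 0.81. Again 11 is the smallest sufficient N.
- rho = 0.5, epsilon = 1: 10 dyads suffice; at 11, lambda = 18.87 and power is 0.89.

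If the seven time points are instead treated as independent samples, 11 per time point gives lambda = 0.1225 × 77 = 9.43 on 6 and 70 df and power 0.57, and 17 per time point are needed for 0.80. The figure of 11 is therefore a within-dyad calculation with positive correlation. The tests named later do not match it.

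**Step 2: the named test against its repeated-measures counterpart.** This was simulated with 20,000 runs per setting. Each value is a dyad effect with variance rho, plus independent error with variance 1 − rho, plus a time-point mean. Three mean patterns were used, each scaled to f = 0.35: a linear trend, a change at a single time point, and a change at the two ends. Ranges are over the patterns. Relative loss is 1 − (Kruskal-Wallis power / Friedman power).

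| Dyads | rho | Kruskal-Wallis true type I error | Kruskal-Wallis power | Friedman power | Relative loss |
|---|---|---|---|---|---|
| 11 | 0.3 | 0.0095 | 0.40–0.44 | 0.60–0.64 | 31–33% |
| 11 | 0.5 | 0.0018 | 0.33–0.38 | 0.77–0.81 | 53–57% |
| 11 | 0.7 | 0.0001 | 0.26–0.32 | 0.95–0.97 | 67–72% |
| 20 | 0.3 | 0.0084 | 0.82–0.84 | 0.92–0.93 | 9–11% |
| 20 | 0.5 | 0.0014 | 0.80–0.84 | 0.98–0.99 | 15–18% |
| 20 | 0.7 | below 0.0001 | 0.78–0.82 | 1.00 | 18–22% |

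For example, with 11 dyads, rho = 0.5 and the linear pattern: 1 − 0.376/0.806 = 53%. Friedman's own type I error stayed at 0.043 to 0.049. At rho = 0 Kruskal-Wallis is valid (type I error 0.044 at 11 dyads) and loses nothing, so the problem comes entirely from the correlation.

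The simulated data are normal, whereas the article reserves these tests for non-normal data. Both tests use ranks only, so any common monotone transformation of the values, such as one producing log-normal skew, leaves the table unchanged.

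**Step 3: two time points.** This used 4,000 runs and illustrative shifts of 0.9 SD (11 dyads) and 0.65 SD (20 dyads).

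| Dyads | rho | Mann-Whitney true type I error | Mann-Whitney power | Signed-rank power |
|---|---|---|---|---|
| 11 | 0.3 | 0.023 | 0.48 | 0.57 |
| 11 | 0.5 | 0.012 | 0.49 | 0.73 |
| 11 | 0.7 | 0.004 | 0.51 | 0.91 |
| 20 | 0.3 | 0.022 | 0.49 | 0.61 |
| 20 | 0.5 | 0.008 | 0.50 | 0.75 |
| 20 | 0.7 | 0.002 | 0.52 | 0.94 |

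**The case against.** The case for leaving the text alone has several parts.

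- **The primary analysis is sound.** It uses mixed models. This stands, and it confines the point to secondary outcomes that are not normally distributed.
- **The error is in the safe direction.** This also stands: no excess of false positives follows. The cost is missed changes.
- **The loss is modest if recruitment holds.** With all 20 dyads analysable, Kruskal-Wallis keeps about 0.8 power at f = 0.35. This stands too. A reader might infer that more than half the power is lost as a matter of course. That is true only near the 11-dyad minimum with a correlation of about 0.5 or more, and the article gives no correlation.
- **The t-test and ANOVA have paired and repeated-measures forms.** Correct. The article does not say unpaired, so only the non-parametric tests and the chi-square are plainly mismatched.
- **Mother-infant pairing is respected for SC and HRV.** Correct for the synchrony step. It does not remove the repetition over time points.
- **A full analysis plan may name other tests.** This does not answer the point, because the article does not leave the choice open. It names tests that do not fit.

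A reader might also infer that the third hypothesis, "The neurophysiological responses are correlated to the infant’s pain reaction, parent’s gaze, and social and musical interactions", is left without a valid test because of these test names. The documents do not support that. The section names no association method, but this is a separate matter of detail that a fuller plan may supply. The general sentence cannot be read as a closed list either, since the same section has just assigned mixed models and wavelet coherence to the primary hypothesis.

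**Conclusion.** The point holds in a limited form. The non-parametric tests named for non-normal data are independent-samples tests, which contradicts both the one-group, seven-time-point design and the repeated-measures basis of the sample size. The chi-square sentence refers to groups that the article does not define.

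For an assumed correlation of 0.3 to 0.7 and f = 0.35, Kruskal-Wallis runs at about 1% or less instead of 5%. Its relative power loss against Friedman runs from about 9% (20 dyads, correlation 0.3) to about 72% (11 dyads, correlation 0.7). These sizes rest on the assumed correlation, equal correlation between time points, and the reading of 0.35 as Cohen's f. The mismatch itself rests on none of these.

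**What to change.** In the Statistical analyses section:

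1. Replace Mann-Whitney with the Wilcoxon signed-rank test and Kruskal-Wallis with the Friedman test. Alternatively, use a mixed model with a dyad random intercept and time point as a fixed effect, in line with the primary analysis.
2. State that the t-test is paired and the ANOVA is repeated-measures.
3. Delete the chi-square sentence, or define the groups it is meant to compare.

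This changes wording only. It needs no new data and no change to the sample size. The article schedules data analysis for 2028, so the correction can be made before any outcome is analysed, which avoids a choice of test after the data are seen.
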